# Effects of starting one lung ventilation and applying individualized PEEP right after patients are placed in lateral decubitus position on intraoperative oxygenation for patients undergoing thoracoscopic pulmonary lobectomy: study protocol for a randomized controlled trial

**DOI:** 10.1186/s13063-024-08347-8

**Published:** 2024-07-22

**Keywords:** One lung ventilation, Individualized PEEP, Video-assisted thoracic surgery, Atelectasis, Recruitment maneuvers, Oxygenation

## Abstract

**Background:**

For patients receiving one lung ventilation in thoracic surgery, numerous studies have proved the superiority of lung protective ventilation of low tidal volume combined with recruitment maneuvers (RM) and individualized PEEP. However, RM may lead to overinflation which aggravates lung injury and intrapulmonary shunt. According to CT results, atelectasis usually forms in gravity dependent lung regions, regardless of body position. So, during anesthesia induction in supine position, atelectasis usually forms in the dorsal parts of lungs, however, when patients are turned into lateral decubitus position, collapsed lung tissue in the dorsal parts would reexpand, while atelectasis would slowly reappear in the lower flank of the lung. We hypothesize that applying sufficient PEEP without RM before the formation of atelectasis in the lower flank of the lung may beas effective to prevent atelectasis and thus improve oxygenation as applying PEEP with RM.

**Methods:**

A total of 84 patients scheduled for elective pulmonary lobe resection necessitating one lung ventilation will be recruited and randomized totwo parallel groups. For all patients, one lung ventilation is initiated the right after patients are turned into lateral decubitus position. For patients in the study group, individualized PEEP titration is started the moment one lung ventilation is started, while patients in the control group will receive a recruitment maneuver followed by individualized PEEP titration after initiation of one lung ventilation. The primary endpoint will be oxygenation index measured at T4. Secondary endpoints will include intrapulmonary shunt, respiratory mechanics, PPCs, and hemodynamic indicators.

**Discussion:**

Numerous previous studies compared the effects of individualized PEEP applied alone with that applied in combination with RM on oxygenation index, PPCs, intrapulmonary shunt and respiratory mechanics after atelectasis was formed in patients receiving one lung ventilation during thoracoscopic surgery. In this study, we will apply individualized PEEP before the formation of atelectasis while not performing RM in patients allocated to the study group, and then we’re going to observe its effects on the aspects mentioned above. The results of this trial will provide a ventilation strategy that may be conductive to improving intraoperative oxygenation and avoiding the detrimental effects of RM for patients receiving one lung ventilation.

**Trial registration:**

www.Chictr.org.cn ChiCTR2400080682. Registered on February 5, 2024.

**Supplementary Information:**

The online version contains supplementary material available at 10.1186/s13063-024-08347-8.

## Background

Nowadays, most video-assisted thoracic surgeries require one lung ventilation to avoid contamination of the contralateral lung by secretions and blood from the operated lung and to facilitate surgical exposure. Patients receiving one lung ventilation in lateral decubitus position are prone to develop atelectasis in the dependent lung due to decreased thoracic compliance and compression of the mediastinum and abdominal contents [1]. Increased atelectatic regions in the dependent lung not only give rise to lung injury, but also increase intrapulmonary shunt, which aggravates hypoxemia [2]. Therefore preventing formation of atelectasis during one lung ventilation has become a crucial problem.

Many randomized controlled trials discovered that a lung protective ventilation strategy involving low tidal volume combined with PEEP and RM could significantly reduce driving pressure, peak airway pressure, plateau pressure anddead space, alleviate intrapulmonary shunt, improve oxygenation and reduce the incidence of PPCs; whereas the ventilation mode that incorporated low tidal volume combined with PEEP but without RM had limited effects on oxygenation and incidence of PPCs [1, 3–7].

However, RM could cause delayed pulmonary inflammatory response and lung injury [1]. Furthermore, the high airway pressure required to reopen collapsed alveoli during RM could lead to overinflation of lung units, and thus could shift blood flow to atelectatic lung units, disrupt gas exchange, and induce inflammatory reaction [8].

Although RM have become an element of lung protective ventilation, no consensus has been reached concerning the airway pressure and the length of time needed to perform RM [9]. In the study of Miura and colleagues, in which response to RM was defined as increase in end expiratory lung volume equaling to or exceeding 20% of baseline level, half of the patients involved were responsive to RM. Compared to responders, the non-responders’ proportion of atelectatic lung tissue is much smaller, limiting the effect of RM on improving oxygenation and enlarging lung volume [10]. Consequently, the benefit of RM performed before formation of atelectasis was limited.

Among patients receiving general anesthesia with muscle relaxants, three in four would develop atelectasis [11]. According to CT results, atelectasis usually forms in gravity dependent areas no matter in which position patients are placed [11]. Therefore, in supine position, atelectasis usually forms in the dorsal part of the lung, while in lateral decubitus position, atelectasis tends to develop in the lower flank of the lung. Accordingly, after patients are switched from supine to lateral decubitus position, the collapsed lung units in the dorsal part of the lung will reexpand, while atelectasis will slowly develop in the lower flank of the lung. So it’s reasonable to believe that development of atelectasis could be prevented by applying sufficient PEEP before lung units in the lower flank start to collapse.

In many previous studies, patients received two lung ventilation without PEEP after being placed in lateral decubitus position, and one lung ventilation wasn’t initiated until pleura opening [3, 4, 6]. Immediately after initiation of one lung ventilation, RM were performed followed by individualized PEEP (iPEEP) titration. Because of the long interval between the initiation of two lung ventilation in lateral decubitus position and the initiation of one lung ventilation, during which period patients were ventilated with fraction of inspired oxygen (FiO_2_) of 100% and without PEEP, most patients had already developed atelectasis in the lower flank of the dependent lung and consequently necessitated RM to reopen collapsed alveoli.

The study of Edmark et al. which enrolled patients with body mass index (BMI) over 35 kg/m^2^ undergoing elective laparoscopic gastric volume reduction surgery discovered that patients who received 10cmH_2_O continuous positive airway pressure (CPAP) or PEEP during anesthesia induction and preoxygenation without RM exhibited preserved oxygenation throughout the entire duration of anesthesia until emergence [12]. Because obese patients under general anesthesia are more susceptible to developing atelectasis compared to their normal weight counterparts [13], we believe that atelectasis formation may be prevented throughout the whole duration of surgery by applying sufficient PEEP while not performing RM.

Numerous studies confirmed the advantages of iPEEP for patients undergoing one lung ventilation under general anesthesia [5, 12, 14, 15]. However, up till now, no consensus has been reached concerning the appropriate method for iPEEP titration. When tidal volume remains constant, driving pressure mainly correlates with Cstat; so PEEP could be titrated to maximize Cstat [15]. According to the result of a meta-analysis, the oxygenation of patients receiving driving-pressure-guided lung protective ventilation during one lung ventilation was significantly higher than those ventilated with other strategies [5]. Since increase in driving pressure strongly correlates with increased incidence of PPCs, we believe that for patients receiving one lung ventilation, titrating PEEP to optimize Cstat has its advantages.

This trial is going to test the hypothesis: the ventilation strategy of starting one lung ventilation and then iPEEP titration immediately after adjustment of the position of the double lumen tube in lateral decubitus position while not performing RM is not inferior to the strategy of initiating one lung ventilation right after pleura opening and then performing RM followed by iPEEP titration in the aspects of improving patients’ oxygenation, respiratory mechanics and reducing the incidence of PPCs during one lung ventilation.

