### Intervention

For patients in both groups, one lung ventilation is initiated after readjusting the position of the double lumen tube in lateral decubitus position, The lumen to the independent lung remain closed to air during the interval between intubation to pleural opening. It’s opened to air for 2 min after pleural opening, and subsequently connected with the apneic oxygen insufflation device, which delivers pure oxygen to the independent lung at a constant rate of 5L/min. The dependent lung is ventilated in pressure-controlled volume-guaranteed (PCV-VG) mode, with a tidal volume of 4-5 ml/kg, I:E set to 1:2, and respiratory rate adjusted to maintain end-expiratory carbon dioxide within the range of 30-40 mmHg.

For patients in the study group, individualized PEEP titration is started right after the start of one lung ventilation. The initial PEEP is set to 15cmH_2_O. Subsequently PEEP is lowered at steps of 2cmH_2_O every 3 min. Before changing the level of PEEP, Cstat is calculated according to the formula (Cstat = VT/Pplat-PEEP). When Cstat ceases rising with the continuous lowering of PEEP but starts to drop, the previous PEEP level at which Cstat reaches its zenith is selected as the ideal PEEP (Fig. 2). Then PEEP is elevated to ideal PEEP and kept constant towards the end of the procedure.

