**Fig. 2 Fig2:**
[figure not shown]
Individualized PEEP titrated to maximize Cstat. *RM* ventilator driven recruitment maneuver, *PEEP* positive end expiratory pressure, *iPEEP* individualized PEEP, *Cstat* static lung compliance

For patients in the control group, PEEP is set to zero before pleural opening. Right after pleural opening, the dependent lung undergoes RM in pressure-controlled mode, driving pressure set to 20cmH_2_O, PEEP initially set to 5cmH_2_O and raised at steps of 5cmH_2_O and maintained for 10 breathing cycles for each step. When PEEP reaches 20cmH_2_O and plateau reaches 40 cmH_2_O, PEEP level is maintained for 15 breathing cycles towards the end of RM (Figs. 3 and 4), followed by iPEEP titration consistent with that of the study group.

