### Sample size calculations

The primary endpoint of this study is oxygenation index measured at T4. According to literature [16], oxygenation index for patients inhaling pure oxygen and under well oxygenated conditions during TLV usually ranges between 350-400 mmHg and drops to 150-200 mmHg after patients are switched to OLV. Therefore, during OLV, changes in oxygenation index within the limit of 50 mmHg would be clinically insignificant. Thus, the cut-off value for inferiority is set to 50 mmHg. In other words, in our study, if oxygenation index measured at T4 of the study group is below that of the control group, but the difference between that of the two groups is within 50, then the ventilation strategy of the study group is not inferior to that of the control group in terms of improving intraoperative oxygenation. We set probability of type 1 error at α = 0.025, probability of type 2 error at β = 0.20, and power value at 0.80; a sample size of 38 is calculated for each group by using PASS 11.0 software. Considering a 10% removal and dropout rate, a final sample size of 42 is required for each group.

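### The hypothesis compares against a control that starts one lung ventilation at pleura opening, but the Methods start it in both arms after lateral positioning, so its timing is not tested

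*Protocol article*

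**What the plan says.** The hypothesis at the end of the Background defines both strategies. The study strategy is "starting one lung ventilation and then iPEEP titration immediately after adjustment of the position of the double lumen tube in lateral decubitus position", without a recruitment maneuver. The claim is that it "is not inferior to the strategy of initiating one lung ventilation right after pleura opening and then performing RM followed by iPEEP titration".

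The Methods paragraph of the abstract gives a common start: "For all patients, one lung ventilation is initiated the right after patients are turned into lateral decubitus position". The Intervention section says the same: "For patients in both groups, one lung ventilation is initiated after readjusting the position of the double lumen tube in lateral decubitus position".

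The control-group paragraph of the Intervention section (after the Figure 2 caption) adds: "For patients in the control group, PEEP is set to zero before pleural opening". It continues: "Right after pleural opening, the dependent lung undergoes RM in pressure-controlled mode". Titration then follows by the same procedure as in the study group.

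The title names an early start of one lung ventilation together with individualized PEEP as the thing whose effects are studied. In Sample size calculations, the primary endpoint is the oxygenation index at T4, and "the cut-off value for inferiority is set to 50 mmHg".

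**The concern.** A non-inferiority claim is always relative to a named comparator. Here the hypothesis names one and the Methods deliver another. The difference lies in a factor, the start of one lung ventilation, that the title and the Background hypothesis treat as part of the intervention.

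The stake is interpretation. A reader of the title and hypothesis would take a positive result as support for starting one lung ventilation early. A reader of the abstract's Background, which sets PEEP without recruitment before atelectasis forms against PEEP with recruitment, could take it as support for leaving out recruitment. Under the Intervention section, the first reading is not tested and the second is not isolated.

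There are practical consequences too. The start of one lung ventilation in the control arm determines its recorded duration (Study visits and data collection). It also bears on the inclusion criterion comparing the lengths of one and two lung ventilation (Study population). Finally, it fixes the period to which the hypoxemia rule for one lung ventilation, with its exclusion from the final analysis, applies (Protocol deviation).

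**Working it through.** The point rests on text, so the check sets the places side by side.

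| Feature of the control arm | Background hypothesis | Abstract, Methods | Intervention section |
|---|---|---|---|
| Start of one lung ventilation | right after pleura opening | after turning, all patients | after tube readjustment in lateral position, both groups |
| PEEP before pleural opening | not stated | not stated | zero |
| Recruitment maneuver | after one lung ventilation starts at opening | after one lung ventilation starts; opening not mentioned | right after pleural opening |
| PEEP titration | after recruitment | after recruitment | after recruitment |

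1. **Where the texts agree.** Control recruitment precedes titration in all three. The abstract's silence on pleural opening is compatible with the other two.

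2. **Where they conflict.** Only the first row conflicts. One lung ventilation in the control arm cannot start both at pleura opening and at tube readjustment before it.

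3. **What differs between arms under each version.** Under the hypothesis, the arms differ in the start of one lung ventilation, the timing of titration and recruitment. Under the Intervention section, the start is common to both. The arms differ in PEEP before opening (being titrated or set to its titrated level, against zero), the timing of titration and recruitment. Three elements change together, so the design cannot attribute a result to any one of them.

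4. **Where the hypothesis's comparator may come from.** The Background describes earlier studies in which "one lung ventilation wasn’t initiated until pleura opening", followed by recruitment and titration. That regimen matches the comparator in the hypothesis, not the control arm in the Intervention section.

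5. **Whether other text settles it.** Study endpoints defines the control arm's T3 as five minutes into ventilation in the lateral position, without saying whether on one lung or two. Mechanical ventilation gives a tidal volume for two lung ventilation in the lateral position, but that could apply to other phases of the case. The hypothesis in Objectives and design does not mention control timing. Figures 1 and 4 are not available here and could not be checked.

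6. **Numerical consequence.** None follows. The planned 38 per group, raised to 42, and the 50 mmHg margin do not depend on which version is right.

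**The case against.** The strongest reply is that a workable control regimen exists. The abstract and the Intervention section agree with each other, and the control-group paragraph spells out what happens up to and after pleural opening. The hypothesis in Objectives and design fits that regimen, so the outlier is one clause in the Background. This stands: the control arm is not undefined, and the Objectives and design hypothesis remains testable. It does not remove the conflict. The Background clause is the document's most explicit statement of what is compared with what, and the title shares its emphasis on starting one lung ventilation.

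A second reply is that the plan already speaks of comparing strategies, both in the Background hypothesis and in Sample size calculations, and that the abstract's hypothesis makes timing explicit through its reference to atelectasis formation. This also stands in part. A trial of strategies need not isolate recruitment. The two strategies must still be the same ones throughout the document, and they are not.

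A reader might go further and infer that the control is put at a disadvantage, because zero PEEP on pure oxygen in the lateral position promotes atelectasis, and that non-inferiority is therefore easier to reach. The documents do not support this for the primary endpoint. The Discussion's remark about rapid atelectasis concerns two lung ventilation in earlier studies. The control arm's recruitment and titration are complete before T4. Nothing in the text shows or quantifies a deficit remaining at T4.

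**Conclusion.** The inconsistency is real and stands in the current text. It is limited to when one lung ventilation starts in the control arm and to what the trial may therefore conclude. If run as the Intervention section describes, the trial compares two bundles that differ in pre-opening PEEP, titration timing and recruitment. It says nothing about the timing of one lung ventilation.

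The effect cannot be given in mmHg. A reader might take the ranges in Sample size calculations (350-400 mmHg on two lungs, 150-200 on one), find a gap of 150 to 250 mmHg (350 − 200 and 400 − 150), and set it against the margin. That comparison fails. Such a gap could at most concern the control value at T3, while the margin is defined for T4, when the control arm is on one lung ventilation under either version. The ranges are also general literature values, not predictions for this arm.

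The conclusion assumes that the figures not shown do not resolve the conflict. It takes no position on which timing is right.

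**What to change.** - Reconcile the abstract, the Background hypothesis and the Intervention section into one description of what the control arm receives between lateral positioning and pleural opening. Choosing the timing is for the investigators.
- State in Study endpoints whether the control arm's T3 is measured on one lung or two.
- Carry that description into the title and hypothesis, and check Figures 1 and 4 against it.
- Word the hypothesis and planned conclusion as a comparison of the two whole strategies, listing every element that differs. If early one lung ventilation is common to both arms, do not attribute the result to it. Do not attribute the result to omitting recruitment alone.

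The cost is protocol wording and a short amendment. No patients are added, and the endpoint, margin and sample size are unchanged. As recruitment was planned from March 2024, the team should also confirm which control regimen has been delivered to any patients already treated, so that the reconciled text describes what was done.

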### Statistical analysis

The research team will cooperate with medical statisticians to analyze data after completing the trial. SPSS 20.0 software will be applied for data processing. Dropout or lost to follow up cases will be reported. Per-protocol analyses will be applied for all data. Under circumstances of missing values, multiple imputation shall be conducted. Kolmogorov–Smirnov analysis will be performed to discern normally distributed data. Normally distributed data will be presented as mean $$\pm$$ standard deviation (SD), while discrete data will be presented as median and interquartile range. Independent-samples T test will be adopted for univariate analysis of normally distributed data. Pearson correlation test will be used to test the linear relationship between two variables. Mann–Whitney U test will be applied for discrete data. Categorical variables will be expressed as relative risk ratio and assessed by Fisher’s exact test or chi-square tests, if applicable. 95% CI will be employed to express confidence level of all parameters. *P* value < 0.05 shall be defined as statistically significant.

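### The non-inferiority hypothesis covers oxygenation, respiratory mechanics and PPCs, but the design gives a margin and a sample size for oxygenation index at T4 only

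*Protocol article*

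**What the plan says.** The last paragraph of the Background sets out what the trial will test: that the strategy without a recruitment maneuver (RM) "is not inferior to the strategy of initiating one lung ventilation right after pleura opening" with RM. It names the domains as oxygenation, "respiratory mechanics and reducing the incidence of PPCs during one lung ventilation".

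The section Sample size calculations is narrower. "The primary endpoint of this study is oxygenation index measured at T4", and "the cut-off value for inferiority is set to 50 mmHg". Its conclusion is that the study strategy would be "not inferior to that of the control group in terms of improving intraoperative oxygenation". The error rate is given as follows: "We set probability of type 1 error at α = 0.025". With power 0.80 this leads to 38 per group, and to 42 after an allowance for dropout.

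The Abstract and the section Study endpoints list respiratory mechanics and PPCs as secondary. No margin is given for either.

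The section Statistical analysis names the t test, the Mann–Whitney test, and Fisher's exact or chi-square tests, with significance at P < 0.05. "Categorical variables will be expressed as relative risk ratio", and 95% CIs are promised for all parameters. Those intervals are not tied to a margin.

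**The concern.** Non-inferiority is shown when a confidence interval excludes a margin fixed in advance. A difference test asks another question, and a non-significant result from it is compatible with a large true disadvantage. Two of the three domains in the hypothesis have only difference tests, so the trial as described cannot confirm the hypothesis for them.

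PPCs matter most here. The primary endpoint is an intraoperative blood gas measure, while PPCs are clinical complications. The Background itself reports that, in earlier trials, low tidal volume with PEEP but without RM did little for oxygenation or PPC incidence. Whether omitting RM costs patients anything in PPCs is therefore a live question, and the wording of the hypothesis should not suggest that this trial can settle it.

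There is also a mismatch of timing. The hypothesis places PPCs in the period of one lung ventilation, whereas the section Study visits and data collection records them as postoperative.

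**Working it through.** **1. The hypothesis beside the design**

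| Domain | In the non-inferiority hypothesis | Margin | Sample size | Named analysis |
|---|---|---|---|---|
| Oxygenation index at T4 | yes | 50 mmHg | 38 per arm (42 with dropout) | non-inferiority conclusion in the sample size section |
| Respiratory mechanics | yes | none | none | t test or Mann–Whitney, P < 0.05 |
| PPC incidence | yes | none | none | Fisher or chi-square, P < 0.05 |

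**2. The plan's own figure.** Inputs from the article: margin 50 mmHg, α = 0.025 (sidedness not stated; taken as one-sided), power 0.80, 38 per arm. No SD is stated, so 38 can only be solved backwards. From n = 2·SD²·(1.960 + 0.842)²/50², n = 38 gives SD = (50/2.802) × √(38/2) ≈ 77.8 mmHg at most. A whole-number SD of 77 returns 38 and 78 returns 39. A t-based calculation returns 38 for an SD of 76 to 76.5. The figure is thus consistent with an SD near 77 and no true difference, and it concerns oxygenation only.

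**3. PPCs with 38 per arm.** The article gives no expected PPC rate and no PPC margin. The rates of 10%, 20% and 30%, the 10-point margin and the 15-point disadvantage below are all assumptions. Where equal true rates p are assumed:

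- SE of the risk difference = √(2p(1−p)/38) = 0.0688 / 0.0918 / 0.1051.
- 95% CI half-width = 1.96 × SE = 13.5 / 18.0 / 20.6 points.
- Power at a 10-point margin = Φ(0.10/SE − 1.96) = Φ(−0.51) / Φ(−0.87) / Φ(−1.01) = 31% / 19% / 16%.
- Smallest margin with 80% power = 2.802 × SE = 19 / 26 / 29 points.
- Number per arm for 80% power at 10 points = 2p(1−p) × 2.802²/0.10² = 142 / 252 / 330, rounded up.

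Using all 42 per arm changes little: the half-widths become 12.8 / 17.1 / 19.6 points and the power 33% / 21% / 17%.

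**4. What a non-significant Fisher test would mean.** Suppose the study arm is truly 15 points worse (10% v 25%, 20% v 35%, 30% v 45%). Exact enumeration of the two-sided Fisher test with 38 per arm gives a non-significant result in 69% / 76% / 80% of trials. With 42 per arm the figures are 64% / 74% / 76%.

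**5. Respiratory mechanics with 38 per arm.** On a standardised scale, the margin with 80% power is 2.802 × √(2/38) = 0.64 SD. This matches the oxygenation margin on the SD implied in step 2 (50/77.8 = 0.64), as it must with the same n, α and power. A margin of 0.5 SD would need 63 per arm, and one of 0.3 SD would need 175. Whether 38 is enough depends on a margin that the article does not give.

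**The case against.** The strongest reply is that the operative sections are already in order. Oxygenation index at T4 is primary, mechanics and PPCs are secondary, and the only stated non-inferiority conclusion is limited to oxygenation. PPCs will get a risk ratio, and 95% CIs are promised throughout. The wide hypothesis stands in one closing sentence of the Background. The Abstract and the section Objectives and design word the aim differently, and neither claims non-inferiority on PPCs. Low power for a secondary endpoint is normal, and margins for secondary endpoints may be left to an analysis plan that is not shown.

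Much of this stands, and it is why the remedy is small. It does not remove the mismatch. The sentence is introduced as the hypothesis that the trial will test, and it disagrees with other sections of the same article. An analysis plan could add margins, but it could not make 38 to 42 per arm adequate for PPCs at a 10-point margin under the assumed rates.

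Three stronger readings are tempting, and the document does not support them:

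- A reader might infer that a non-significant Fisher test will be reported as PPC non-inferiority. The article does not say so. It only leaves this open, because it gives no other decision rule for PPCs.
- A reader might infer that the trial is too small for respiratory mechanics as well. Step 5 of the working does not show that.
- A reader might take PPCs to be the only outcome that matters to patients. The section Study endpoints also lists ICU transfer, length of stay and adverse events.

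**Conclusion.** The point holds as an inconsistency within the article: non-inferiority is hypothesised in three domains and designed for in one. That rests on the text alone and needs no assumption.

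For PPCs the planned size is also inadequate for a non-inferiority claim, with power of 31%, 19% and 16% at 38 per arm. Those figures depend on the assumed rates and 10-point margin, and on equal true rates in the two arms. For respiratory mechanics only the missing margin is established.

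This should be corrected because it governs what the trial may conclude. It does not affect the primary comparison or the number of patients.

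**What to change.** - Reword the hypothesis in the Background so that non-inferiority, and any conclusion of it, is confined to oxygenation index at T4. The sample size section already does this.
- Describe respiratory mechanics and PPCs as secondary outcomes, reported as estimates with the 95% CIs already promised. A risk difference for PPCs beside the planned risk ratio would help the reader but is optional.
- Add one sentence stating that a non-significant difference in these outcomes will not be reported as non-inferiority.
- Remove the reference to one lung ventilation as the period for PPCs, since they are collected postoperatively.

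The cost is a few sentences in the article and in the analysis plan. No patients, data or procedures are added. The price is a narrower claim: the trial would no longer set out to show non-inferiority on mechanics or PPCs.
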